## Abstract

**Background:**

Current treatments for adolescents with substance use disorder (SUD) have had only limited success. In recent years, research has underlined the role of self-regulatory processes and impulsivity in the development and maintenance of SUD in adolescents. Mindfulness has gained much attention due to its capacity to influence self-regulatory processes, particularly in adult populations. Initial studies have shown the potential of mindfulness-based approaches in younger SUD patients. The aim of the present clinical trial is to evaluate the added treatment effect of a mindfulness-based group psychotherapy (“Mind it!”) for adolescents with SUD in comparison to the current standard treatment. Moreover, we seek to explore the feasibility of the intervention and possible mediators of treatment effects.

**Methods/design:**

There will be *N* = 340 participants aged between 13 and 19 years who are receiving child or adolescent psychiatric or psychotherapeutic inpatient or day treatment targeting their SUD and who have reported substance use 30 days before detoxification and do not show acute psychotic or suicidal symptoms at baseline. The study is a prospective randomized controlled multi-center trial in which patients are assessed: (1) after completing a prior detoxification phase (*t*_0_), (2) at 4 weeks (*t*_1_), (3) at 8 weeks (*t*_2_), and (4) at 6 months after *t*_2_ (*t*_3_). Participants in the intervention group will receive mindfulness-based group psychotherapy in addition to their existing treatment regime. The primary outcome is substance use in the past 30 days at follow-up based on the Timeline Followback self-report. Secondary outcomes include craving, severity of dependence, and abstinence motivation. Mindfulness, impulsivity, and emotion regulation will be analyzed as possible mediators of treatment effects.

**Discussion:**

This trial is expected to provide evidence of the added effect of a novel, safe, and feasible treatment option for adolescents with SUD.

**Trial registration:**

German Register of Clinical Studies, DRKS00014041. Registered on 17 April 2018.

## Background

The use of alcohol and illegal drugs and their associated detrimental health outcomes amount to 19.737 disability adjusted life years (DALYs) in Europe [1]. Adolescence is a vulnerable period for the development of substance use disorders (SUDs). Specifically, when individual substance use patterns exacerbate, the risks for negative health and psychosocial outcomes increase [2, 3]. Prevalence rates of SUDs in children and adolescents from population-based samples have not yet been measured in Germany, but some previous research allows for estimates: 10 to 15% of German males aged 14–24 were found to have alcohol dependence or misuse according to DSM-IV criteria. Cannabis abuse was reported by 5.5% and cannabis dependence by 2.2% in the same sample [4]. National health report data show that 34% of patients with substance dependence are younger than 25 years [5] and about 35,000 patients under 20 years receive costly inpatient treatment due to diagnoses relating to “mental or behavioral disorders due to psychoactive substance use” (ICD-10, chapter F10-F19). In essence, SUDs in children and adolescents are an enormous public health burden.

Although progress has been made for both access to and availability of pharmacological and psychotherapeutic SUD treatments [6, 7], current research on the effects of treatment in SUD patients for various age groups shows disappointing results. Relapse rates range between 50% and 81% across various delivery modes, such as highly structured outpatient settings [8], inpatient settings [9], and combined psychotherapeutic and pharmacological treatments [10]. Specific research on SUD patients who are minors is scarce [11], but would be greatly desirable [7].

In recent years, there has been significant research on (neuro-)biological mechanisms for the development of substance use in minors. The research into mechanisms focuses on self-regulatory processes, specifically, motivational aspects such as reward responsiveness, delay discounting, and impulsivity [12, 13]. However, the findings on SUD mechanisms have barely been translated into treatment programs, which may be a reason for the limited success of SUD treatment in minors [6, 13–16].

Preliminary evidence from research-informed treatments links self-regulatory models of SUD to mindfulness-based approaches, because mindfulness targets several aspects of self-regulation [6, 12, 13, 17]. Mindfulness is defined as bringing full awareness to present-moment experiences in an accepting, non-judgmental, and open-minded way [18]. Mindfulness skills are associated with cognitive and affective stability and flexibility, adaptive coping, and reduced cue-reactivity towards stress-induced cravings [12, 19]. Initial neuroimaging [19, 20] and clinical studies [21] provide evidence that mindfulness skills can help SUD patients. Mindfulness brings attention to highly automated and minimally controlled habits, which are often involved in craving and substance use relapse. Mindfulness practice can help people to become aware of craving and substance use habits. This opens opportunities for modifying reactions instead of following established stimulus–response behaviors, which may involve modifying unpleasant sensations or emotions with substance use. This could reduce the risk of relapse in SUD patients.

Sanger and Dorjee [22] produced strong neuropsychological evidence for the positive effects of mindfulness practice in adolescence. Affective self-regulation and coping skills were enhanced by changes in prefrontal brain functioning. The current literature suggests that mindfulness practice impacts affective stability and attentional control and may, therefore, be useful in SUD treatment [23].

The effects of mindfulness-based interventions in adult clinical populations are well documented. Mindfulness-based interventions target different patient groups, such as mindfulness-based stress reduction for chronically ill patients [24, 25], mindfulness-based cognitive therapy (MBCT) for depressed patients [26] and mindfulness-based relapse prevention (MBRP) for SUD patients [27–29]. Even in comparison to active control groups, these interventions were able to reduce legal and illegal substance use [30–32], cravings [13, 17], and relapse rates [30–32]. Up to now, no unwanted side effects of mindfulness-based interventions have been reported for relevant target groups.

Clinical evidence for underage patient groups is scarce. Several clinical studies focus solely on specific clinical aspects of mindfulness-based interventions such as outpatient aftercare [30] or sleep improvement [33]. One work focuses on co-occurring post-traumatic stress disorder and addiction [34]. Another study was a qualitative pilot study, which limits its generalizability [35]. Evidence for the use of mindfulness-based interventions for child and adolescent substance use is not as clear as in adult patients [36–38]. However, initial results show that mindfulness practice helped to complement cognitive behavior therapy approaches in children with emotion regulation deficits [39].

According to current evidence, mindfulness-based interventions are safe and effective. Mindfulness practice can help to improve attentional control, depressive symptoms, anxiety, rumination, externalizing problem behavior, social skills, and stress. Moreover, SUD-specific problems, such as emotional self-regulation and craving, have been shown to improve through mindfulness-based approaches. As yet, there are no mindfulness-based treatments for younger SUD patients that have adapted tested mindfulness-based SUD approaches in a developmentally appropriate way. There is a need for high-quality clinical trials that focus on the reduction of substance use as the primary outcome to evaluate the full potential of mindfulness-based treatment approaches in underage SUD patients. To our knowledge, there have been no such randomized controlled clinical trials.

With the current study, we aim to answer the following two questions:Is there an additive treatment effect for young SUD patients who receive complementary mindfulness-based group therapy, as shown by higher 30-day abstinence rates 6 months after treatment, in comparison to participants receiving standard youth psychiatric SUD inpatient treatment? In secondary exploratory analyses, we want to see if the effects of the mindfulness-based group therapy on treatment are mediated through factors that are related to the content of the intervention, such as impulsivity, (trait-)mindfulness, emotion regulation, and perceived stress.Can a mindfulness-based treatment manual for SUD adolescents be implemented and used to support and complement current SUD treatments effectively in inpatient youth psychiatric settings?

## Methods/design

### Design

The current trial is a subproject run by the consortium IMAC-Mind (Improving Mental Health and Reducing Addiction in Childhood and Adolescence through Mindfulness: Mechanisms, Prevention and Treatment), which focuses on the use of mindfulness-based approaches for different SUD populations. The current study is a prospective randomized controlled trial with treatment as usual for the control group.

### Sample

Study participants will be patients diagnosed with a SUD (ICD-10: F10-F19) aged 13 to 19 years who are currently receiving inpatient or daycare clinical treatment for that condition and who have completed detoxification. Subjects are diagnosed by treating clinicians and their diagnoses are verified in additional clinical interviews by study personnel. Patients will be excluded from the study if they show symptoms of acute suicidality, schizophrenia, or other disorders with acute psychotic symptoms. Further exclusion criteria are an IQ under 70, insufficient knowledge of German by either patients or their parents or guardians, and no substance use in the 30 days prior to detoxification. Patients’ medication is not an exclusion criterion but will be carefully documented.

### Measurement

Participants are asked questions in structured clinical interviews and they complete questionnaires. Their hands are scanned so that we can calculate the 2D:4D ratio (*t*_0_ only), and they undergo a computerized assessment for several neuropsychological tasks at four points within the study process: after detoxification and before randomization and the following SUD treatment phase (*t*_0_), 4 weeks into treatment (*t*_1_), 8 weeks after *t*_0_ (*t*_2_), and 6 months after *t*_2_ (*t*_3_). Figure 1 gives an overview of the measures used.

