### Sample size calculation

Based on prior research [29, 31, 32], we expect to detect a small to medium-sized effect of *d* = 0.36 for our primary outcome. We calculated the sample size using G*Power [76], with a two-sided alpha level of 0.05 and a study power of 80%. The required sample will comprise 246 participants (123 both in the control group and in the intervention group). To achieve this sample size, we seek to screen *N* = 340 patients for eligibility for the trial (Fig. 1).

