### Analyses

Data will be analyzed according to the CONSORT statement [40]. A detailed statistical analysis plan will be prepared and finalized before breaking the blind. Descriptive statistics will be determined for the intention-to-treat population according to treatment assignment. The intention-to-treat population consists of all randomized patients. The primary hypothesis is that the intervention is superior to treatment as usual according to the number of days with substance use within the past 30 days 6 months after the end of the intervention (*t*_3_). A mixed negative binomial regression will be performed based on the intention-to-treat population with treatment group, time, interaction between treatment group and time, and recruitment center as fixed effects, the number of days with substance use within the past 30 days at baseline as a covariate, and patient and therapy group as random effects. The contrast of the treatment group at *t*_3_ will be interpreted in a confirmatory manner. We will report adjusted group differences with corresponding 95% confidence intervals and *p* values. Mixed models are more robust against missing values than models without random factors and yield unbiased estimates under the missing at random assumption. For model diagnostics, a systematic examination of factors associated with loss to follow-up will be conducted. Missing values will be imputed in a sensitivity analysis by the multiple imputation method. Additionally, the primary analysis will be conducted on the per protocol population. The following subgroup analyses will be planned. The secondary outcomes will be analyzed in an exploratory manner with appropriate models with the same covariates and fixed and random effects as in the primary analysis. Multiple mediation models for identifying the mechanisms of intervention effects (with a focus on behavioral measurements of self-regulation and mindfulness) will be used [77]. The safety end points will be determined with a mixed logistic regression. Interim analyses are not planned. The two-sided type I error will be set at 5%. Statistical analyses will be carried out with SPSS, Version 21 (IBM Corp., Armonk, NY).

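### The confirmatory model is valid but adjusts for one patient-level baseline value; prespecifying a few more t0 values would be a cheap gain in precision, of a size the article cannot establish

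*Protocol article*

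**What the plan says.** The Analyses section specifies a mixed negative binomial regression for days of use. The fixed effects are treatment, time, their interaction and center; patient and therapy group are random effects; and "the number of days with substance use within the past 30 days at baseline as a covariate" is added. Center is the stratification factor (Procedure), so the baseline use count is the only patient-level baseline value. Secondary outcomes are to be modelled with the same covariates.

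The Sample section lists "no substance use in the 30 days prior to detoxification" among the exclusion criteria, so everyone enters with at least one use day in that window.

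The Measurement section puts t0 "after detoxification and before randomization and the following SUD treatment phase" and says that interviews, questionnaires and neuropsychological tasks are given at all four time points. It does not name the scales. The schedule by scale is in Fig. 2, which is not shown in the text at hand, so collection of each scale at t0 is an inference, though a natural one.

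On missing data, the Analyses section relies on missing at random in the mixed model. It says under model diagnostics that "a systematic examination of factors associated with loss to follow-up will be conducted", and it adds multiple imputation as a sensitivity analysis. It promises a detailed analysis plan before the blind is broken.

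**The concern.** Adjusting for a prognostic pre-randomisation value narrows the interval of the treatment contrast and needs no new data. The article itself gives reasons to think some t0 measures could be prognostic. The Background describes mechanism research on "motivational aspects such as reward responsiveness, delay discounting, and impulsivity", and the section on neuropsychological testing says impulsivity and related traits are linked to adolescent substance use. The section on secondary outcomes lists dependence severity and abstinence motivation among the measures of SUD symptoms. None of these enters the confirmatory model.

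A second consideration is missing data. If patients with, say, weaker abstinence motivation are lost more often from one arm than from the other, and also use more at t3, then a model without motivation can give a biased t3 contrast. Patients are not blinded, so loss that differs by arm is conceivable. The planned examination of loss to follow-up is a diagnostic, and the article describes no step by which its findings would enter the confirmatory model.

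**Working it through.** **Inputs from the article (Sample size calculation):** d = 0.36, two-sided alpha 0.05, power 80%, 123 per arm, 246 in total. **Assumed, because the article gives neither:** the share R² of the variance left by the planned model at t3 that the added t0 values explain, and the rate and pattern of loss to follow-up.

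**1. Reproducing the stated sample size.** For a two-sample t-test the noncentrality is d × √(n/2) with 2n − 2 degrees of freedom. With n = 123 this is 0.36 × √61.5 = 2.823 on 244 degrees of freedom, and power is 80.3%. The smallest n per arm that reaches 80% is 123, so 246 is confirmed. This is an unadjusted calculation, so the sample size does not depend on extra covariates.

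**2. Gain from adjustment.** The residual SD shrinks by √(1 − R²), so the standardised effect becomes 0.36/√(1 − R²) and the effective sample size 246/(1 − R²).

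| Assumed R² | √(1 − R²) | Standardised effect | Effective N | Interval narrower by | Power |
|---|---|---|---|---|---|
| 0 | 1 | 0.3600 | 246 | 0% | 80.3% |
| 0.05 | 0.9747 | 0.3694 | 259 | 2.5% | 82.3% |
| 0.10 | 0.9487 | 0.3795 | 273 | 5.1% | 84.2% |
| 0.20 | 0.8944 | 0.4025 | 308 | 10.6% | 88.2% |

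The gain is about 2, 4 or 8 percentage points. This is the two-means approximation on which the sample size rests, not the mixed count model.

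**3. If some patients are lost.** Suppose 246 are randomised and 20% are lost (assumed), which leaves 0.8 × 123 = 98.4 per arm. By the normal approximation, which gives 80.6% with no loss, power is 71.4% unadjusted, 75.9% at R² = 0.10 and 80.6% at R² = 0.20.

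**4. Precision and bias in a count model.** A negative binomial simulation used 246 patients, a true log rate ratio of −0.40, dispersion 1, a baseline covariate that is always in the model, and one further t0 covariate X with log-rate coefficient 0.20, 0.35 or 0.50. Each setting had 600 runs. Dropout, where present, was about 25–28%. All of these values are assumptions.

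| Strength of X | SD of estimate, no dropout: without X → with X | Mean estimate without X, dropout depends on X equally in both arms | Mean estimate without X, dropout depends on X in one arm only | Same, with X in the model |
|---|---|---|---|---|
| 0.20 | 0.142 → 0.137 | −0.403 | −0.432 | −0.389 |
| 0.35 | 0.153 → 0.142 | −0.405 | −0.478 | −0.400 |
| 0.50 | 0.163 → 0.136 | −0.410 | −0.505 | −0.398 |

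With equal dependence in both arms the bias without X is at most 0.01. With dependence in one arm only it is 0.03, 0.08 or 0.11 on the log scale, and adding X removes it to within about 0.01. The simulation used t3 only, without the t1 and t2 outcomes or a therapy-group effect, so it shows the mechanism and not the size of bias to expect in the planned analysis.

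**The case against.** The strongest reply is that nothing here is an error. Adjusting for the stratification factor and the baseline value of the outcome is a standard and valid choice, and 246 was derived without any adjustment. That stands.

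Three stronger readings are tempting and are not supported.

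- **That the article names these measures as relapse predictors.** The Background passage concerns mechanisms in the development of use in minors. The description of standard treatment says that patients are motivated, not that motivation predicts outcome. The article gives the SDS and age no predictive role, and it presents impulsivity as a secondary outcome and possible mediator. The link it does draw to relapse is for craving and automated habits.
- **That the one covariate can explain little because most patients sit near daily use.** The entry rule removes only zero use days. Counts from 1 to 30 remain possible, and no distribution is given.
- **That the confirmatory contrast will be biased by dropout.** The article gives no loss rate or pattern, and with equal dependence in both arms the bias is negligible. The mixed model over t1 to t3 and the multiple imputation already give partial cover, and the imputation predictors may be listed in the analysis plan, which is not shown. The cover is only partial: t1 and t2 fall within or at the end of the eight treatment weeks, while t3 is six months later, and the imputation is only a sensitivity analysis.

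It is also fair to say that the change is not entirely free, as set out under the fix. That impulsivity is a proposed mediator is no obstacle: its t0 value precedes randomisation, so adjusting for it does not remove any effect that runs through later change.

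**Conclusion.** The point holds as a cheap improvement, not as a defect. The model is valid, the sample size stands, and no result would be wrong for want of the change. The covariate set of the confirmatory analysis is nevertheless stated in this article, and it leaves unused pre-randomisation information that is probably already collected.

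The expected gain is about 2, 4 or 8 power points if the added t0 values explain 5%, 10% or 20% of the remaining variance, and near nil if they are not prognostic. The documents cannot say which applies. Better protection against dropout bias is a conditional benefit: it needs values that are prognostic and a loss to follow-up that depends on them differently by arm. The conclusion also assumes that the scales are in fact given at t0, which Fig. 2 would confirm.

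**What to change.** Before unblinding, prespecify in the Analyses section and the analysis plan a short set of t0 values as fixed effects in the primary model, for example SDS score, HEISA goal item, UPPS total and age. Include the same set in the multiple-imputation model. Report the model as now written as a sensitivity analysis.

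The cost is small but not zero:

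- No new data are needed, and there are four extra parameters if each value is scored linearly.
- The SDS asks about a particular substance, so a rule is needed for a single score in users of several substances.
- The HEISA item is a choice among goals, so its scoring must be fixed.
- Missing t0 values need a simple rule that ignores treatment arm, so that all randomised patients stay in the analysis.
- The secondary models use the same covariates, so the change carries over to them and should be checked there.

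Craving could also be considered, but it is measured with the CCS-7 for cannabis and with visual analogue scales for other substances, so it would first need a common scale. The set has to be fixed in advance: covariates added to a confirmatory model after unblinding would look data-driven.

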**Fig. 1 Fig1:**
[figure not shown]
Flow diagram for the Mind it! trial. SUD Substance use disorder

### Methods against bias

The study follows the CONSORT statement for randomized controlled trials [40]. This includes the publication of a study protocol and the study’s public registration (German Register of Clinical Studies, DRKS00014041). The procedures for study inclusion and assessment (obtaining informed consent, handling of questionnaires, clinical records, and clinical interviews) are performed by study personnel who remain blind to the participants’ randomization to either the intervention group (mindfulness-based group intervention “Mind it!”) or the control group (treatment as usual) and who are not involved in providing treatment. Blinding of patients is not possible due to their (non-)participation in the mindfulness-based group intervention. Self-reports regarding substance use are validated through urinalyses, which are routinely taken as part of SUD treatment and are extracted from medical records. Diagnostic assessments are based on highly standardized measurement tools and clinical information is provided by experienced clinicians. All study personnel are trained to conform to current guidelines and regulations (e.g., data safety). Questionnaire data will be computerized by trained staff using the EpiData software to ensure the high quality of the entered data. Additionally, a clinical research organization will monitor adherence to the study protocol and overall study quality. A data and safety monitoring board will oversee study procedures, recruitment, and data flow twice yearly and advise project staff when necessary.

